### Anamnestic questions

Besides the regular anamnestic questions (general history, medication, family history, general demographics, present complaints, etc), patients are asked for:

• Height of the parents

• Timing of thelarche, menarche, and menarche of the mother

• History of the shoe size

### Physical examinations

Regular physical exam of the back is done including inspection, determination of the range of motion, and the Adam's forward bending test.

Measurements are taken for total height, sitting height, lateral arm span, foot length, shoe size, and weight. Subischial leg length is calculated by distracting sitting height from total height. All length measurements are measured three times per visit, to the nearest mm, and an average will be calculated.

Measurement of total height is done by use of a stadiometer constructed according to the internationally agreed assignments and with digital reading. The patient is asked to stand upright with bare feet, having their feet parallel together, and the back of the head touching the upright steel rod against the wall. The child is encouraged to stretch out to the maximum by applying gentle pressure upward under the mastoid process, with the recorder watching to see that the heels are not off the ground. The recorder measures height by lowering the horizontal bar of the stadiometer, making contact with the top of the head. No height corrections are made for curve magnitude.

Sitting height is measured with similar height measuring equipment, while the patient sits on a table with exact known height. The patient is asked to sit straight and the legs hanging freely from the ground. Furthermore, measurement of sitting height is similar to the measurement of total height.

Lateral arm span is measured using a tape measure, from the end of the long finger of one hand, to the end of the long finger on the other hand, with arms maximally outstretched. The tape measure is confirmed to the wall, and the patient is asked to stand straight against the wall and stretch out the arms horizontally.

Foot length and shoe size are measured with a validated calliper in which length in mm and standardized shoe size can be determined. Each patient's bare left and right foot are measured individually while standing full weight bearing. The patient stands in the calliper with the back of the heel against the stationary arm, and the movable arm is brought into contact with the tip of the longest toe. The length is measured to the nearest mm, and shoe size to the nearest half-size.

Weight is measured on a validated scale to the nearest 0.1 kg.

Secondary sexual characteristics are determined by the Tanner criteria for breast development and pubic hair development. Determination of the Tanner stage is performed by a trained female observer. Furthermore, patients are asked for self evaluation of the secondary sexual characteristics according to a figure of the Tanner stages. Patients and their parents point out the figure of which they think is most representative. The reliability of self evaluation will be determined by calculating the correlation between the stages of the patient and the trained observer.

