### Secondary sexual characteristics

Another hallmark of maturation is de development of secondary sexual characteristics, often classified by Tanner. Thelarche, the first stage of secondary breast development, marks the beginning of puberty and usually takes place 1 year before the peak growth velocity of height[4,11,29,30]. Girls typically reach peak growth velocity of height between stage 2 and 3 of breast development and pubic hair development. The pubertal or Tanner stages are good measurements of maturity. However, most orthopaedic surgeons are uncomfortable in evaluating secondary sexual characteristics with their patients, and self assessment of patients is said to be unreliable. Timing of menarche, the first menstrual period, can be used in girls, but most often takes place 1 year after PHV and is therefore always retrospective. It is assumed that the timing of menarche of the child is closely related to the timing of menarche of the mother. When the mother can recall the timing of her menarche, some predictions can be made for the timing of menarche of the child, and therefore for the timing of the pubertal growth spurt. However, it is still unknown how accurate this relationship is.

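### The Tanner self-evaluation is described as a choice by patients and parents, so its reported reliability may not be that of the patient's own rating

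*Protocol article*

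**What the plan says.** Two places in the protocol article bear on this.

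- **Background, Secondary sexual characteristics.** The article calls Tanner stages good measures of maturity but notes that most orthopaedic surgeons are uncomfortable assessing them. It adds that "self assessment of patients is said to be unreliable".
- **Methods/design, Physical examinations.** Four statements follow one another:
  - The reference: "Determination of the Tanner stage is performed by a trained female observer".
  - The measure under test: "patients are asked for self evaluation of the secondary sexual characteristics according to a figure of the Tanner stages".
  - How the rating is obtained: "Patients and their parents point out the figure of which they think is most representative".
  - The analysis: "The reliability of self evaluation will be determined by calculating the correlation between the stages of the patient and the trained observer".

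The article describes no separate patient-only rating, no separate parent rating and no rule for a patient and parent who disagree.

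**The concern.** A reliability coefficient belongs to a particular rater using a particular procedure. Here the label and the analysis name the patient as rater, while the procedure names the patient and the parents. If the recorded stage is a family choice, the coefficient says how well families agree with the trained observer. It does not say how well adolescents do.

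This matters because the Background doubts self-assessment by patients, and this check is the only part of the study that addresses that doubt. The Discussion also tells clinicians that they can choose the indicators feasible in their own practice. A reader who is reluctant to perform Tanner staging could take the coefficient as evidence for or against asking the adolescent, when it was obtained with a parent taking part. With visits every six months, the same ambiguity would recur at each one.

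**Working it through.** The plan gives no figure on this point, so there is none to reproduce. The check is a comparison of the statements, followed by a short calculation of whether the direction of any effect could be known.

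**Step 1: who is the rater in each statement?**

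| Statement | Rater named |
|---|---|
| Background doubt | patients |
| Request for the rating | patients |
| Procedure | patients and their parents |
| Analysis | the patient, against the trained observer |

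The procedure is the odd one out. It has plural raters, a shared opinion and a single figure chosen, which on a plain reading is one joint choice. Yet what enters the analysis is described as "calculating the correlation between the stages of the patient and the trained observer".

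**Step 2: does another section resolve it?** Anamnestic questions, Outcome measurements, and Sample size and statistical analysis contain no patient-only Tanner rating. Outcome measurements lists Tanner stage without mentioning self-evaluation.

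**Step 3: could the direction of the effect be known?** The document gives no error SD for either rater, so the following inputs are assumptions. Let the patient's rating error have SD σ₁ = 0.6 stage and the parent's σ₂ = 0.8 stage, with correlation ρ between them. Suppose that the joint choice is their average, before rounding to a stage. Its error variance is

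(σ₁² + σ₂² + 2ρσ₁σ₂) / 4,

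to be compared with the patient-alone variance of 0.6² = 0.36.

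- ρ = 0: (0.36 + 0.64 + 0) / 4 = 0.25. This is smaller, so the joint choice correlates better with the observer.
- ρ = 0.5: (0.36 + 0.64 + 0.48) / 4 = 0.37. This is practically equal.
- ρ = 0.8: (0.36 + 0.64 + 0.768) / 4 = 0.442. This is larger, so the joint choice correlates worse.
- Patient defers fully to the parent: 0.8² = 0.64. This is larger still.

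The step from error variance to correlation takes both raters' errors as unrelated to the true stage and to the observer's error. The sign changes within a plausible range of assumptions, so the document supports no statement of size or direction.

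**The case against.** The strongest reply is that the sentences on either side of the procedure both name the patient as rater. The procedure sentence does not state that the choice is made jointly, and it does not exclude each party pointing separately. A condensed article may also leave the recording form to a fuller document. This stands in part: joint rating is the plain reading, but it is not established. It does not remove the problem, because separate pointing would still leave unstated how the parents' choice is used.

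A second reply is that a family-assisted rating may be just what this clinic wants. Patients are aged 8 to 17, and parents already help with shoe-size recall. That is reasonable. The fault would then be the label, and relabelling would cure it.

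A reader might be tempted to go further in three ways, none of which the document supports:

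- **That the patient's own answer is lost for good.** The article does not describe what is recorded, so this is inference.
- **That self-rating may follow, and be influenced by, the observer's staging.** This rests only on silence about the order within the visit, which an article commonly omits.
- **That reliability will be overstated by some number of percentage points.** Any such number needs assumed rater errors, and its sign can reverse. Percentages of exact agreement would also not be the correlation that is planned.

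**Conclusion.** The point holds in a limited form. The procedure as described does not cleanly yield the quantity that the article says it will report. The rater in the procedure differs from the rater in the label and in the analysis, and no patient-only rating is described. The reported reliability may therefore not be that of the patient's own self-assessment.

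This rests on reading the procedure sentence as one shared choice. If patients and parents choose separately, what remains is a need to say whose choice enters the correlation.

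The size and direction of any effect are unknown. The point is minor and confined to a secondary reliability check. The Tanner stage itself comes from the trained observer, and neither the main growth and curve-progression analyses nor the sample-size reasoning is shown to depend on the self-rating.

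**What to change.** Have the patient mark the figure first and alone. Record any parental choice on a separate form. Correlate each separately with the trained observer, and use only the patient's mark for the statement about self-evaluation.

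If a family rating is what is wanted, keep the procedure but name the measure and its conclusion as a patient-and-parent rating.

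The first option costs one extra form per visit and no additional staff. The second costs only a change of wording, but leaves the Background's doubt about patients' own ratings unanswered.

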### Sample size and statistical analysis

The maximum sample size of this study is not determined on beforehand, as the study is aimed to proceed for the coming years.

We aim to perform a first preliminary analysis of the longitudinal data when patients have a follow up of at least 2 years. As the expected number of new patients is 60 each year, it will take 2.5 years for 30 patients to reach a follow up of at least 2 years. Taking a loss to follow up into account due to surgical treatment, we expect to be able to analyse the complete data of at least 25 patients. The statistical power will increase with a longer follow up and more patients. The number of 25 patients was checked whether it was large enough to obtain a good prediction model according to the criteria of Knofczynski and Mundfrom [33]. With a significant large influence of 4-5 predictor variables (as is expected in this study) and a squared multiple correlation coefficient between 0.5 and 0.7 between 25 and 65 patients should be included. Therefore the first preliminary analysis will be performed using data of 25 patients.

Individual data charts are made, and results of each parameter are plotted against the growth velocity of total body height and the curve progression.

All statistical calculations are made using SPSS (SPSS Inc, Chicago USA). Pearson correlation coefficients are computed for each individual possible related parameter against the peak growth velocity and the curve progression (Figure 5). A correlation above 0.70 is believed to be clinically relevant. To be able to interpret this value in a reliable way, we will report the confidence intervals as well.

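### Reliability of Tanner self-rating is to be judged by a correlation, which cannot show systematic over- or under-rating

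*Protocol article*

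**What the plan says.** Under Physical examinations, two ratings are made on the same ordinal scale. For the first, "Determination of the Tanner stage is performed by a trained female observer". For the second, "Patients and their parents point out the figure of which they think is most representative". The two are compared as follows: "The reliability of self evaluation will be determined by calculating the correlation between the stages of the patient and the trained observer". The type of correlation is not named there, and no value is set at which self-rating would count as reliable.

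The background section Secondary sexual characteristics records a prior doubt, "self assessment of patients is said to be unreliable", and gives the landmark against which a stage is read: "Girls typically reach peak growth velocity of height between stage 2 and 3 of breast development and pubic hair development".

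Under Sample size and statistical analysis one coefficient is named, but for another purpose: "Pearson correlation coefficients are computed for each individual possible related parameter against the peak growth velocity and the curve progression". The only threshold, "A correlation above 0.70 is believed to be clinically relevant", follows directly and belongs to the same predictor analyses. No kappa, percent agreement, intraclass correlation or check of systematic difference appears anywhere in the article.

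**The concern.** Asking how reliable a self-rated stage is, with a trained observer as reference, is chiefly a question of agreement: does the patient land on the observer's stage, and if not, in which direction and how far off? A correlation answers a different question, namely whether patients whom the observer places higher also place themselves higher. Patients who all over-rate by the same amount can correlate perfectly with the observer and never agree.

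The article gives reasons why this could matter in practice. It notes that many orthopaedic surgeons are uneasy about doing the staging themselves, and its Discussion invites clinicians to pick the indicators that are feasible for them. A reader could therefore take a high correlation as support for using the self-rated stage instead of an examination. For a girl at stage 2 or 3, an error of one stage in the wrong direction puts her on the other side of the growth landmark.

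**Working it through.** **No figure to reproduce.** The article gives no sample size, expected value or threshold for this comparison. The check therefore uses constructed data. The stage distributions and error patterns below are assumptions. Only the size of 25 comes from the article ("Therefore the first preliminary analysis will be performed using data of 25 patients"), and it is used only to scale the illustration.

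**Invariance.** Let X be the observer's stage and Y = X + c the self-rated stage. Then Cov(X, Y) = Var(X) and Var(Y) = Var(X), so Pearson r = 1 for any c. The ranks are unchanged, so Spearman is also 1. The argument does not depend on which of the two is meant.

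**Formulas.** Exact agreement is the share with Y = X. Kappa = 1 − D_obs / D_exp, where D is the mean disagreement, observed and as expected from the two margins. Disagreement is 0/1 for unweighted, |X − Y| for linear and (X − Y)² for quadratic weights.

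**Example A.** Observer stages 1, 2, 3, 4 in 6, 7, 7, 5 patients; all self-rate one stage higher.
- Pearson: 1.1264 / √(1.1264 × 1.1264) = 1.00
- Exact agreement: 0 of 25 = 0%; mean signed difference +1.0
- Unweighted kappa: 1 − 1 / 0.7984 = −0.25
- Linear-weighted kappa: 1 − 1 / 1.4384 = 0.30
- Quadratic-weighted kappa: 1 − 1 / 3.2528 = 0.69

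**Example B.** Five patients at each of stages 1 to 5; all self-rate one stage higher, capped at 5.
- Pearson: 1.6 / √(2.0 × 1.36) = 0.97; Spearman 0.97
- Exact agreement: 5 of 25 = 20%; mean signed difference +0.8
- Unweighted kappa: 1 − 0.8 / 0.8 = 0.00
- Linear-weighted kappa: 1 − 0.8 / 1.6 = 0.50
- Quadratic-weighted kappa: 1 − 0.8 / 4.0 = 0.80

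**Comparison C, unbiased.** Stages uniform over 1 to 5; 80% exact, 10% one stage up, 10% one stage down, held within 1 to 5.
- Pearson: 1.92 / √(2.0 × 2.0) = 0.96
- Exact agreement 84%
- Linear-weighted kappa: 1 − 0.16 / 1.6 = 0.90

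**Comparison D, mild bias.** Stages uniform over 1 to 5; 20% rate one stage too high, capped.
- Pearson: 1.92 / √(2.0 × 1.9744) = 0.97
- Exact agreement 84%
- Linear-weighted kappa: 1 − 0.16 / 1.6 = 0.90

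| | r | Exact agreement | Linear-weighted kappa |
|---|---|---|---|
| A: all +1, stages 1–4 | 1.00 | 0% | 0.30 |
| B: all +1, stages 1–5, capped | 0.97 | 20% | 0.50 |
| C: unbiased noise | 0.96 | 84% | 0.90 |
| D: mild over-rating | 0.97 | 84% | 0.90 |

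The correlation does not separate A and B from C and D; exact agreement and linear-weighted kappa do.

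**Who crosses the landmark.** Under a uniform over-rating of one stage, only patients truly at stage 2 move across the boundary between stages 2 and 3: 7 of 25 (28%) in A and 5 of 25 (20%) in B. Errors from 1 to 2 or from 3 to 4 do not cross it.

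**The case against.** Several points on the other side are sound.

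- **It is a side check.** The Tanner stage listed under Outcome measurements is the one that Physical examinations assigns to the trained observer. Nothing says that the self-rated stage enters the correlations, the regression or the algorithm. A reader might infer that the prediction analyses are compromised; the article does not support that.
- **No cut-off is stated.** A reader might infer that an unusable self-rating will be declared reliable, perhaps by applying the 0.70 threshold. That threshold concerns predictors, so such a declaration is a possible consequence and not a written rule. What remains is that no cut-off on r could reveal a shift.
- **A shifted rating is not necessarily useless.** As its own covariate in a linear regression, an uncapped constant shift is absorbed by the intercept. The harm arises when the self-rated stage stands in for the observer's stage or is read against a stage landmark. The article makes that use plausible but does not state it.
- **A one-stage error does not in general move a patient past the peak.** It does so only for those next to the boundary, and the article's statement is about girls and what is typical.
- **A and B are extremes.** The article supports no particular bias, and under the mild bias of D both statistics look favourable.
- **Dependence on spread is not peculiar to correlation.** A wide maturity range raises r, but weighted kappa moves as well: for the same uncapped shift, linear-weighted kappa is 0.17 with 8, 9 and 8 patients at stages 1 to 3, and 0.32 with 6, 7, 6 and 6 at stages 1 to 4.

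These points limit the consequence. They do not make correlation a measure of agreement.

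**Conclusion.** The point holds as a limited one. The article itself fixes correlation as what determines the reliability of self-rating, so this is a stated choice and not a detail left to an analysis plan. Pearson and Spearman cannot detect systematic misrating. How far this could mislead depends on the assumed stage spread and bias: in the uniform one-stage examples, r of 0.97 to 1.00 goes with 0 to 20% exact agreement. If bias is absent or mild, the conclusion would be much the same with either approach. An absolute-agreement intraclass correlation would respond to a shift, but the text does not mention one. The main aims are untouched. The change is worth making because a conclusion on reliability is announced and the named statistic alone cannot support it.

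**What to change.** Base the reliability conclusion on agreement, separately for breast and pubic hair stage:

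- the cross-table of self-rated against observer stage, with misclassification across stages 2 and 3 shown explicitly;
- percent exact agreement and the mean signed stage difference;
- weighted kappa with 95% CI, the weights stated in advance. Linear weights are preferable here, since quadratic weights still give 0.69 and 0.80 in examples A and B, but this is a judgement.

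Because visits recur every six months, the same patient can contribute several pairs, and an ordinary kappa interval treats these as independent. Use one prespecified visit per patient or an interval clustered by patient. The correlation may be kept as a supplement.

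The cost is a few sentences and slightly more analysis of ratings that are already collected. The reliability figure may turn out less favourable than a correlation would have been.

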### X-ray examinations

Since a clinically important increase in curve severity exists between morning and evening [31], all X-ray examinations are taken in the morning using a standardized X-ray protocol. Brace treated patients are required to remove their brace the morning of the X-ray examination.

All X-ray examinations are performed with a new ultra low dose 2D/3D digital X-ray system (Biospace Med, Paris, France).

This system allows for the simultaneous acquisition of two orthogonal planar images in a vertical scanning mode. The gantry is composed of two sets of detectors and X-ray tubes positioned orthogonally and supported by a mobile C-arm. This C-arm moves vertically using a linear scanning technique. The patient is positioned at the intersection of the two X-ray beams which scan the patient vertically, as illustrated in Figure 1. A single scan will simultaneously produce both AP and lateral images of the patient. A huge advantage of making a total body X-ray is that multiple measurements can be performed in just one single X-ray.

**Figure 1 F1:**
[figure not shown]
**Images obtained by the ultra-low dose 2D/3D digital X-ray system used in this study**. The system can provide total body X-rays for AP and lateral planes simultaneously

On the AP X-ray the scoliosis is classified and the Cobb angle is measured according to internationally agreed standards. The length of the scoliotic spine is measured from the upper end-plate of T1 to the lower end-plate of L5 (Figure 2), according to a previously described method by Cheung et al[32]. Furthermore the axial rotation and lateral deviation of each vertebra are determined.

**Figure 2 F2:**
[figure not shown]
**Calculation of the length of the scoliotic spine as described by Cheung et al.** The length is measured from T1 to L5 through the midpoints of all vertebrae and discs.

Determination of the state of the triradiate cartilage is performed on the AP X-ray of the pelvis (open or closed), as well as determination of the Risser stage (stage 1-5).

Skeletal age of the hand and wrist is determined by a trained observer according to the method of Tanner and Whitehouse. Skeletal age of the elbow is assessed by the Sauvegrain method, using a scoring system for four anatomical landmarks of the elbow[28].

